### **8.2.3 Assessment of the causality of AEs**

The Investigator should assess the causal relationship of adverse events to the research. **Causality is binary (reasonably related / unrelated).**

### **8.2.4 Restriction of AEs/SAEs and reporting period of AEs/SAEs**

Given that the study is being conducted in patients with acute ischemic stroke, restrictions on the notification of SAEs to the safety sector of clinical trials have been put in place to account for adverse events which are expected as part of the natural history of the patient population under study.

***Restriction of SAEs (SAE notification form not to be immediately sent to the DSMB but only to be collected in the CRF at the latest at the end of the study participation):***

- *Adverse events related to the procedure (HDT15) under study:*  
There is no expected serious adverse event related to HDT15 in the intervention group of patients.
- *Adverse events related to the disease under study (acute ischemic stroke):*
  - ⇒ Death (as it is expected from epidemiological data),
  - ⇒ Hemorrhagic transformation of the ischemic lesion,
  - ⇒ Stroke recurrence,
  - ⇒ Malignant cerebral infarction,
  - ⇒ Early neurological deterioration,
  - ⇒ Cardio circulatory arrest,
  - ⇒ Cardiogenic shock,
  - ⇒ Myocardial infarction,
  - ⇒ Heart failure,
  - ⇒ Acute pulmonary edema,
  - ⇒ Pulmonary embolism,
  - ⇒ Pneumonia,
  - ⇒ Urinary tract infection,
  - ⇒ Atrial fibrillation,
  - ⇒ Severe arterial hypertension, defined as blood pressure over 180/110 mmHg.
- *Adverse events related to MT and/or intravenous thrombolysis:*
  - ⇒ Arterial dissection,

- ⇒ Artery perforation,
- ⇒ Vasospasm,
- ⇒ Stent occlusion,
- ⇒ Intracranial hemorrhage (sICH), either symptomatic or not,
- ⇒ Cerebral or systemic embolism,
- ⇒ Facial angioedema,

The investigator should notify the sponsor any serious adverse events, not included in the above specified ones, without delay:

- *FROM THE PATIENT'S INCLUSION (date of signature of the 1st consent)*
- *Until the END OF THE PATIENT'S PARTICIPATION*
- No time limit for serious adverse events related to the research (e.g. cancers, congenital malformations occurring in the long term after exposure to the investigational medicinal product...).

### **8.3 Responsibilities of the sponsor**

#### **8.3.1 Declaration to the competent authorities**

The sponsor should expedite the reporting to all concerned investigator(s)/institutions(s), to the Ethics Committee, where required, and to the regulatory authority of all adverse drug reactions that are both serious and unexpected. Such expedited reports should comply with the applicable regulatory requirement(s) and with the ICH Guideline for Clinical Safety Data Management: Definitions and Standards for Expedited Reporting.

#### **8.4 Data Safety Monitoring Board**

The Data and Safety Monitoring Board will provide expertise by periodical review and evaluation of the accumulated study data for participant safety, study conduct and progress; it will also provide recommendations to the Steering Committee concerning the continuation, modification, or termination of the trial.

## **9 STATISTICAL ASPECTS**

### **9.1 Number of subjects needed**

Considering previous data on distribution of acute stroke patients across the ASITN/SIR collateral scale, a sample size of 118 patients (59 patients per group) should yield 80% power to detect a between group difference of 25% (60% in experimental group versus 35% in control group) for the primary endpoint, which is considered of substantial clinical significance, with a bilateral alpha risk of 0.05.

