#### 4.2 Method for randomisation

Central randomisation will be performed by an online, secure, software application (Sealed Envelope; <https://www.sealedenvelope.com>). The group of intervention will be automatically assigned following a pre-established randomisation list completed by the statistician of the study. The allocation ratio between the HDT15 (intervention) and usual position (control) groups will be 1:1. Randomisation will be stratified by site. To take into account the inter-individual heterogeneity in baseline collateral status, randomisation will also be stratified according to score of the National Institute of Health stroke scale (NIHSS) at presentation in the Emergency Room (dichotomised 0 to 5 versus 6 or more), which will be assessed before treatment allocation. Patients with NIHSS 0 to 5 will be considered as having a “minor stroke” despite a M1 occlusion, which will be considered as a surrogate marker of good baseline collaterals.

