### 4.3 Endpoints

#### 4.3.1 Primary endpoint

The **primary endpoint** will be the achievement of **good collateral status**, i.e. grade 3 or 4 on the American Society of Interventional and Therapeutic Neuroradiology/Society of Interventional Radiology (ASITN/SIR) collateral scale, in the HDT15 versus control group, as seen at the beginning of MT. The ASITN/SIR collateral grade will be assessed by a blinded central imaging core lab from the pretreatment diagnostic angiographic runs, routinely performed as the first procedural step of MT. Patients achieving complete or partial recanalization (spontaneous or rt-PA-induced) at the first angiographic assessment during MT will be excluded from the primary outcome analysis, since ASITN/SIR score could not be assigned. Details regarding the assessment of the primary endpoint are available in **paragraph 10.2.2.**

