### **5.3 Premature study exit criteria**

The criterion for premature study exit for a patient is the withdrawal of consent.

Early withdrawal will not affect standard of medical care. Patients with premature exit from the study will not be replaced.

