#### **9.5 Method of taking missing data into account**

Analyses will be performed on data available. There will be no imputation of missing data.

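### Section 9.1 states 80% power for 118 patients, but that is the zero-loss number; it holds for 118 evaluable patients, and 9.1 neither says so nor allows for the post-randomisation exclusions

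*Protocol*

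**What the plan says.** Protocol 9.1 gives one planning statement: "a sample size of 118 patients (59 patients per group) should yield 80% power to detect a between group difference of 25" percentage points. The assumed rates are "60% in experimental group versus 35% in control group) for the primary endpoint", "with a bilateral alpha risk of 0.05". Section 4.2 fixes the ratio: "The allocation ratio between the HDT15 (intervention) and usual position (control) groups will be 1:1". Section 9.1 does not say whether the 118 are randomised or evaluable patients, and it mentions no allowance for losses.

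Section 4.3.1 says that patients with complete or partial recanalisation, whether spontaneous or caused by rt-PA, "at the first angiographic assessment during MT will be excluded from the primary outcome analysis, since ASITN/SIR score could not be assigned". Section 9.2 makes this the modified intention-to-treat set on which the analyses are run. Section 5.1 admits patients with or without intravenous thrombolysis. Section 9.3.2 plans to report the number recanalised in each arm, but no section gives an expected rate.

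On missing data, section 9.5 uses the data available: "There will be no imputation of missing data". On withdrawals, section 5.3 says: "Patients with premature exit from the study will not be replaced". Section 7.4 applies the same rule to refusals of deferred consent, and keeps data collected up to withdrawal.

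**The concern.** Randomisation takes place after the admission vascular imaging (sections 5.5 and 6.1.1). Recanalisation is judged later, at the first angiographic run of the thrombectomy. The exclusion therefore acts on patients who already count towards enrolment, and in a trial that allows thrombolysis it is foreseeable. A run that cannot be graded is a further route to a missing primary endpoint, since section 10.2 requires both arterial and venous phases for grading.

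If 118 has no reserve, each such patient takes the trial below the power stated in 9.1. That figure is the only planning number behind the proof-of-concept conclusion. A null primary result would be read against 80% power, although the analysed set would have supported somewhat less.

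**Working it through.** **Inputs.** From 9.1: p1 = 0.60, p2 = 0.35, difference 0.25, two-sided alpha 0.05, power 80%, 59 per arm. From 4.2: 1:1 allocation. The share lost to recanalisation or a non-gradable run is not in the protocol. It is an assumption, shown here from 2% to 20%.

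**Step 1: reproduce 118.** Unpooled normal approximation:

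n per arm = (1.960 + 0.842)² × [0.60×0.40 + 0.35×0.65] / 0.25² = 7.849 × 0.4675 / 0.0625 = 58.71, so 59 per arm and 118 in total.

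Power at 59 per arm: SE = √(0.4675/59) = 0.0890; 0.25/0.0890 = 2.809; Φ(2.809 − 1.960) = 80.2%.

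The stated figure is reproduced with zero loss. The slack is 59 − 58.71 = 0.29 of a patient per arm, about 0.5%.

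**Step 2: look for a hidden reserve.** The other two-sided formulas all need more than 59 per arm: pooled variance 62, arcsine 62, log-odds-ratio Wald 65, pooled with continuity correction 70. A one-sided pooled calculation would need 49 and would leave room, but 9.1 states a two-sided alpha. No two-sided formula tried leaves an allowance inside 118.

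**Step 3: apply a loss L.** Evaluable patients per arm = 59 × (1 − L). Power = Φ(0.25/√(0.4675/n) − 1.960), the same formula as in step 1. The detectable difference is for 80% power with the control rate held at 35%. The last column is 118/(1 − L), rounded up to a whole patient before equalising the arms.

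| Assumed loss | Evaluable per arm | Power | Detectable difference | Randomised for 118 evaluable |
|---|---|---|---|---|
| 0% | 59.0 | 80.2% | 25 points | 118 |
| 2% | 57.8 | 79.4% | 25 points | 121 |
| 5% | 56.1 | 78.2% | 26 points | 125 |
| 10% | 53.1 | 75.9% | 26 points | 132 |
| 15% | 50.2 | 73.5% | 27 points | 139 |
| 20% | 47.2 | 71.0% | 28 points | 148 |

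**Step 4: compare with the planned test.** Section 9.3.2 uses a Wald test in a logistic model. Exact enumeration of that test, without covariates or site effects, gives 79.2% at 59 per arm, so the starting point is close to the stated 80%. At 56, 53, 50 and 47 per arm it gives about 75, 72, 73 and 69%. These values do not fall smoothly because the data are discrete. The direction agrees with the table.

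**The case against.** **Section 9.1 may mean evaluable patients.** It says only patients, and it gives the power for an endpoint that 4.3.1 says cannot be assigned after recanalisation. That reading is open. It does not remove the defect, because 9.1 would then be missing the number to randomise.

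**A reader might infer that the trial never had 80% power.** The documents do not support this. The shortfall depends on a loss rate that they do not give, and at 2% loss it is under one point.

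**A reader might infer that nobody who is lost is replaced.** The no-replacement rule in 5.3 and 7.4 covers premature exits and refusals of deferred consent. The protocol does not say whether recanalised or non-gradable patients are replaced. Withdrawals add little in any case: the endpoint is read at the start of thrombectomy and data up to withdrawal are kept. The exception is a patient who refuses deferred consent and also objects to use of the data. Section 10.2 standardises the angiographic acquisition, which should limit non-gradable runs.

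**A reader might quote lower figures, such as 67% at 47 per arm.** That value comes from the log-odds-ratio approximation, which already gives 76.7% at zero loss, against 79.2% by exact enumeration. Part of that gap is approximation error and not an effect of exclusions.

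**Section 9.4 foresees a possible reassessment of sample size and power after the 12-month interim analysis.** It does, but the step is optional and is not an allowance in the stated number.

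**This is a proof-of-concept trial reporting an odds ratio with a confidence interval.** That is true, and the interval will show the precision reached. The estimand, the test and the error rate are not affected. This limits the consequence but does not make the stated power correct for 118 randomised patients.

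**Conclusion.** The point stands in this form: 118 is the bare number for 60% vs 35% with no losses, the protocol's own analysis rule removes recanalised patients after randomisation, and 9.1 does not connect the two. The stated 80% holds for 118 evaluable patients.

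The size is conditional on the assumed loss. It is negligible at about 2%, roughly 2 points at 5%, and about 4 to 9 points at 10% to 20% (80.2% falling to 75.9% and 71.0%). These figures assume losses spread equally over the arms, and that 60% and 35% are the rates among the patients analysed. The recanalisation exclusion is the main route of loss. No particular exclusion rate can be called expected from the documents.

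**What to change.** Keep 118 randomised and restate 9.1. Say that 80% is the power with 118 evaluable patients in the modified intention-to-treat set. Then give the power expected after exclusions, with the assumed share of recanalised and non-gradable patients and the basis for it. The rate seen so far, pooled over both arms and without any comparison between them, would serve as that basis. State also whether recanalised patients are replaced. This costs one paragraph and no extra enrolment; the price is a less favourable stated power. The version table in section 1.2 lists a fourth amendment with its date still open, which could carry the change.

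If 118 was intended as the number of evaluable patients, 9.1 must say so and give the number to randomise: about 125 at 5% loss, 132 at 10%, 139 at 15% and 148 at 20%. That means 7 to 30 more patients, with the recruitment time and funding they require, so it is not a wording change only.

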### **9.2 Analysis population**

The intention-to-treat population is defined as all patients included in the study according to the group allocated at randomisation, regardless of eligibility criteria and amount of

intervention received, whether evaluable or non-evaluable for the endpoints. The description of the population at inclusion will be on an intention-to-treat basis.

Analyses will be conducted on a modified intention-to-treat basis (after exclusion of patients achieving complete or partial recanalization at the first angiographic assessment during MT), with a secondary per-protocol analysis of the primary endpoint.

The per protocol population is defined as the modified intention-to-treat population from which patients with major protocol deviations will be excluded. Major deviations will be reviewed in the blind review, during which additional blinded cases may be identified in the intervention group. These will be specified in the statistical analysis plan. Patients will be considered in the actual group. A secondary analysis of the primary endpoint will be performed per-protocol.

The safety population is defined as the population of patients who received the actual intervention. The safety and tolerability criteria will be assessed according to this population.

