## **2.2 Research hypothesis**

We hypothesise that HDT15 (Head down tilt 15°), applied in AIS patients with an LVO, will improve collateral circulation, prolong the survival of the ischemic penumbra and improve the clinical benefit from MT compared with standard of care (usual positioning: 0° to +30°).

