Pre-specified sensitivity analyses will include: (1) per-protocol vs. modified intention-to-treat analysis; (2) inclusion of only those patients with baseline NIHSS  $\geq 6$ ; (3) exclusion of HDT15 patients with tilting duration  $< 50\%$  of the time from randomization to angiographic collateral assessment; and (4) comparison of control arm subgroups ( $0^\circ$  to  $+5^\circ$  vs.  $+6^\circ$  to  $+30^\circ$ ) to HDT15. The number of patients achieving complete or partial recanalization (spontaneous or rt-PA-induced) at the first angiographic assessment during MT will be reported for both arms.

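### Section 9.2 drops patients recanalised at first angiography from analyses in general, against 4.3.1, so 90-day mRS and percent NIHSS change lose randomised patients for a reason that applies only to the collateral grade

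*Protocol*

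**What the plan says.** Two sections of the protocol set the scope of the same exclusion differently.

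- **4.3.1 (Primary endpoint).** Patients found recanalised, wholly or partly, at the first angiographic look "will be excluded from the primary outcome analysis, since ASITN/SIR score could not be assigned". The scope is one analysis, and the reason is specific to one measurement.
- **9.2 (Analysis population).** "Analyses will be conducted on a modified intention-to-treat basis (after exclusion of patients achieving complete or partial recanalization" at that first look). No endpoint is named. The same sentence ties the per-protocol analysis to the primary endpoint but attaches no such limit to the modified ITT set. Full ITT is assigned only to the description of patients at inclusion. Safety and tolerability criteria go to a separate safety population of patients who received the actual intervention.

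Section 9.3.3 describes the analyses of 90-day mRS, percent NIHSS change and admission-to-puncture time without naming a population. On recanalisation itself, 9.3.2 promises a count by arm: "The number of patients achieving complete or partial recanalization (spontaneous or rt-PA-induced", and so on. Section 9.5 rules out imputation.

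**The concern.** A collateral grade cannot be read once the occlusion has gone, so leaving these patients out of the main ASITN/SIR analysis has a stated reason. That reason does not extend to the mRS at three months or to NIHSS change. It does not extend to time to puncture either: a patient identified as recanalised at the first angiographic run has already had the puncture.

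The event that triggers exclusion comes after allocation and after treatment start. Section 6.1.1 starts tilting as soon as possible after randomisation and expects 30 to 90 minutes of it before the primary endpoint is read. Section 2.6 says that a collateral-enhancing therapy is needed to make successful reperfusion with IVT, as well as with MT, more likely. If tilt changes who recanalises before the first run, the patients left in the two arms are no longer comparable by design. The mRS is the clinical efficacy objective in 3.2. Early NIHSS improvement before MT is the most exposed outcome, because a patient who reperfuses before the first run is plausibly among those who improve by then.

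**Working it through.** **1. The plan's own figure.** Section 9.1 states that "a sample size of 118 patients (59 patients per group) should yield 80% power" for "60% in experimental group versus 35% in control group", "with a bilateral alpha risk of 0.05", and section 4.2 sets allocation at 1:1. With the unpooled normal approximation:

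n per arm = (1.960 + 0.842)² × (0.60×0.40 + 0.35×0.65) / 0.25² = 7.85 × 0.4675 / 0.0625 ≈ 58.7, rounded up to 59, so 118 in total.

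The figure reproduces and is not at issue.

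**2. Which population governs each outcome, reading 9.2 literally.**

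| Outcome | Population under 9.2 | Needs an ASITN/SIR grade? |
|---|---|---|
| Baseline description | full ITT | no |
| Good collaterals (primary) | modified ITT | yes |
| 90-day mRS | modified ITT, by default | no |
| Percent NIHSS change | modified ITT, by default | no |
| Admission-to-puncture time (descriptive) | modified ITT, by default | no |
| NIHSS worsening of 4 points or more, SICH, pneumonia, vomiting | safety population | no |

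The conflict with 4.3.1 lies in the three middle rows marked as default.

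**3. Does any primary-endpoint analysis keep these patients?** The per-protocol set is a subset of the modified ITT set. The four sensitivity analyses in 9.3.2 (per-protocol against modified ITT, NIHSS 6 or more, short tilt duration, control-angle subgroups) do not restore them. The head-position analysis is worded for all patients, but it uses the same grade and gives no rule for patients who cannot be graded.

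**4. How large could selection be?** The protocol gives no recanalisation rate, so every rate below is assumed. Suppose tilt has no effect on collaterals and a share g = 0.35 has good collaterals in both arms. Let recanalisation probability be r_g in patients with good collaterals and r_p in the rest. The good-collateral rate among the patients analysed is

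g(1 − r_g) / [g(1 − r_g) + (1 − g)(1 − r_p)].

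| Control r_g / r_p | HDT15 r_g / r_p | Control rate | HDT15 rate | Spurious difference |
|---|---|---|---|---|
| 10% / 10% | 10% / 10% | 35.0% | 35.0% | 0 |
| 15% / 8% | 15% / 8% | 33.2% | 33.2% | 0 |
| 10% / 10% | 20% / 10% | 35.0% | 32.4% | −2.6 points |
| 15% / 8% | 30% / 8% | 33.2% | 29.1% | −4.2 points |
| 10% / 10% | 10% / 20% | 35.0% | 37.7% | +2.7 points |

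**5. An mRS illustration, also assumed.** Take recanalisation of 10% in control and 20% in HDT15, with a good outcome in 75% of recanalised patients and 45% of the others.

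- All randomised, control: 0.10×0.75 + 0.90×0.45 = 48%.
- All randomised, HDT15: 0.20×0.75 + 0.80×0.45 = 51%.
- Modified ITT: 45% in both arms.

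A 3-point difference disappears. The standard error of that difference at 59 per arm is √[(0.48×0.52 + 0.51×0.49)/59] ≈ 9.2 points.

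**6. What an all-randomised check of the primary endpoint would show.** Keep 60% and 35% among patients not recanalised.

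- With 10% recanalised in each arm, the difference is 22.5 points whether recanalisation counts as success (0.64 − 0.415) or as failure (0.54 − 0.315).
- With 10% in control and 20% in HDT15, it is 26.5 points as success (0.68 − 0.415) and 16.5 points as failure (0.48 − 0.315).

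The gap between the two codings measures how far the result depends on the excluded patients.

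**The case against.** The best defence is that 4.3.1 already states the intended scope, so 9.2 is only loosely worded, in a sentence that ends on the primary endpoint. That stands in part: the text is in conflict, and it does not settle that mRS patients will be dropped. But 9.2 is the section that assigns populations, its wording is unlimited, and nothing in 9.3.3 overrides it.

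Several stronger readings are tempting and are not supported.

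- **That every analysis is affected.** It is not. Baseline description is on full ITT, and safety outcomes have their own population, which does not remove recanalised patients. Among the NIHSS outcomes, only percent change is caught.
- **That the exclusion from the primary analysis is itself an error.** It is disclosed, defined in advance and reasoned. Counting recanalisation as success or failure answers a composite question and not the collateral question in 3.1. Extra sensitivity analyses can also be left to the SAP, for which 9.6 provides. With counts by arm, a reader can form crude unadjusted bounds.
- **That the best responders to HDT15 are removed, so the trial is biased against it.** This is one scenario among several. The table above contains shifts in both directions, and zero.
- **That the research hypothesis predicts earlier recanalisation.** Section 2.2 says that HDT15 "will improve collateral circulation, prolong the survival of the ischemic penumbra and improve the clinical benefit from MT". It does not mention the artery opening before thrombectomy. Section 2.6 comes closer, but as a general statement of expected benefit.

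The mRS example also dichotomises an endpoint that the protocol analyses as an ordinal shift, and its 3 points are small beside a standard error of about 9.

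**Conclusion.** Sections 4.3.1 and 9.2 disagree on the scope of the exclusion, and the 9.2 reading is the worse one. It conditions 90-day mRS, percent NIHSS change and the descriptive time to puncture on an event after randomisation, for a reason that does not apply to them. This is a stated rule in conflict with another, not a detail deferred to the SAP.

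The documents do not allow the size or direction of any bias to be derived. If tilt does not affect recanalisation there is no selection bias, only a loss of patients. Under the assumed rates above, the spurious difference in the collateral rate runs from −4.2 to +2.7 points, and the mRS example hides 3 points. Severity is moderate: the trial is a phase 2a/b proof of concept with an angiographic primary endpoint, and the affected outcomes are secondary. The lack of an all-randomised check on the primary endpoint is an opportunity for a cheap addition and not an error.

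**What to change.** **Correction, in 9.2.** Restrict the modified ITT set to the ASITN/SIR endpoint, in line with 4.3.1. State that 90-day mRS, percent NIHSS change and admission-to-puncture time are analysed in all randomised patients by allocated arm, on the data available as 9.5 already provides. This costs about two sentences and no new data. It is best settled before the interim analysis in 9.4, which covers both primary and secondary outcomes.

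**Suggested addition, in 9.3.2.** Add a sensitivity analysis of the primary endpoint in all randomised patients, with recanalisation at the first run counted once as success and once as failure. Report the between-arm difference in recanalisation with its 95% confidence interval beside the counts already promised. The cost is a little more analysis work, and the report should say that these analyses address a composite and not collateral status alone.

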## **6.3 Blinding**

### **6.3.1 Organisation**

Double-blinding of the study intervention is not possible. The Neurologist and Neurointerventionist in charge of the patient will remain in close proximity of the patient during HDT15 application, and cannot be blinded. Similarly, the patient cannot be blinded to the treatment allocation, given the nature of the procedure (HDT15 or flat position). Thus, this study is an open-label trial but with a blinded assessment of all endpoints, including the primary outcome, which will be assessed by a central imaging core lab.

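### The per-protocol rule in section 9.2 contradicts itself: a blind review cannot find extra cases in a named arm, and only the intervention arm is named

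*Protocol*

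**What the plan says.** Section 9.2 starts from a definition that names no arm: "The per protocol population is defined as the modified intention-to-treat population from which patients with major protocol deviations will be excluded". It then describes how deviations are found: "Major deviations will be reviewed in the blind review, during which additional blinded cases may be identified in the intervention group". Two short sentences follow, "These will be specified in the statistical analysis plan" and "Patients will be considered in the actual group".

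The main analysis is on the modified intention-to-treat set, "with a secondary per-protocol analysis of the primary endpoint". Section 9.3.2 lists the same comparison as sensitivity analysis (1), "per-protocol vs. modified intention-to-treat analysis". Sensitivity analysis (3) there is a separate exclusion, openly limited to one arm: "exclusion of HDT15 patients with tilting duration" below half of the time from randomisation to the angiographic assessment.

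On blinding, section 6.3.1 states "Thus, this study is an open-label trial but with a blinded assessment of all endpoints". On the control arm, section 6.2.1 assigns a position for the emergency room and for the angiography table, and section 7.3.2 requires the angle to be recorded in both arms.

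**The concern.** The review sentence cannot be carried out as written. To place a case in the intervention group, the reviewer must know the allocation, and the review is then not blind to it. The protocol does not say whether blind means blind to allocation or to the collateral grade, nor what a blinded case is in an open-label trial.

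The sentence also provides for additional cases in one arm only. Control patients can deviate too, since they have an assigned and recorded position, but nothing parallel is written for them.

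The actual-group sentence adds a second route. Section 9.3.2 foresees HDT15 patients who return to standard positioning because of intolerance. If such a patient is not excluded as a major deviation, the sentence can be read as counting that patient with the controls. Group membership would then depend on events after randomisation.

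At stake is whether the per-protocol result can serve as a check on the main result. If it is built by asymmetric exclusion, it shares that feature with sensitivity analysis (3), and agreement between the two would be weaker corroboration than it appears.

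**Working it through.** **1. The plan's own figure.** Section 9.1 gives 59 per group for 60% versus 35%, two-sided alpha 0.05 and 80% power. The unpooled two-proportion formula reproduces it:

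n = (1.96 + 0.842)² × (0.60×0.40 + 0.35×0.65) / 0.25² = 58.7, so 59 per arm and 118 in total.

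This point does not touch that figure. The 35% control rate and 59 per arm are used below only as a starting point.

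**2. The sentences side by side.**

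- Definition: major deviations are excluded; no arm is named.
- Review: described as blind, yet additional cases may be identified in the intervention group. If blind refers to allocation, the two halves cannot both hold.
- Control arm: position assigned (6.2.1) and recorded (7.3.2), so deviations could be judged there by the same means.
- Grouping: by position actually received, with no statement that patients who received the other arm's position are excluded first.

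**3. Shift from excluding HDT15 patients only, with no true effect.** Let p = 0.35 in both arms, f the share of HDT15 patients removed, and q the good-collateral rate among those removed. Both f and q are assumptions; the protocol gives neither.

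HDT15 rate among those kept = (p − f·q) / (1 − f)

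| f | q | HDT15 rate kept | Shift (points) |
|---|---|---|---|
| 10% | 15% | (0.35 − 0.015)/0.90 = 37.2% | +2.2 |
| 10% | 10% | (0.35 − 0.010)/0.90 = 37.8% | +2.8 |
| 20% | 15% | (0.35 − 0.030)/0.80 = 40.0% | +5.0 |
| 20% | 10% | (0.35 − 0.020)/0.80 = 41.25% | +6.25 |
| 10% or 20% | 35% | 35.0% | 0 |
| 10% | 50% | (0.35 − 0.050)/0.90 = 33.3% | −1.7 |
| 20% | 50% | (0.35 − 0.100)/0.80 = 31.25% | −3.75 |

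If the same share with the same outcome mix is removed from both arms, the difference is zero.

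**4. What this does to a test.** I enumerated the two-sided Wald test of the log odds ratio, without site or NIHSS adjustment. With 59 per arm and no exclusion it rejects in 4.7% of trials. With 59 controls and 53 HDT15 patients kept (f = 10%, q = 15%) it rejects in 6.2%; with 47 kept (f = 20%, q = 10%), in 9.8%. These are the favourable-direction cases only.

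**5. Shift from regrouping.** If those patients are moved to control instead, the control rate becomes (p + f·q) / (1 + f).

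- f = 10%, q = 15%: control (0.35 + 0.015)/1.10 = 33.2%; gap 37.2 − 33.2 = +4.0 points.
- f = 20%, q = 10%: control (0.35 + 0.020)/1.20 = 30.8%; gap 41.25 − 30.8 = about +10 points.
- q = 35%: gap 0.
- q = 50%: control (0.35 + 0.050)/1.10 = 36.4% at f = 10%, gap 33.3 − 36.4 = about −3 points; control (0.35 + 0.100)/1.20 = 37.5% at f = 20%, gap 31.25 − 37.5 = about −6 points.

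For the same patients, moving them gives a larger gap than removing them.

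**The case against.** The strongest reply is that the operative definition is neutral between arms and the review sentence is only clumsy. A reader might infer that controls are not reviewed, or that every extra exclusion falls on HDT15. The text says neither: additional cases may be found in the intervention group, and control deviations are still excluded under the general rule. That part of the reply stands.

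A reader might also infer that the per-protocol result is biased, and in favour of HDT15. The protocol does not support that. The direction is set by the outcome rate among those removed, which is not given. Neurological worsening is a listed reason for stopping the tilt, which makes poor collaterals among those removed plausible. However, the protocol does not say that failing to keep the position is a per-protocol deviation. The calculation also starts from 59 per arm and ignores patients removed for early recanalisation.

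Nor is this the only secondary look at the primary endpoint. Section 9.3.2 pre-plans an analysis of time-weighted head angle across all patients, which keeps intolerant HDT15 patients in and partly covers the same worry.

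Finally, the detailed criteria are left to the statistical analysis plan, so their absence here is no fault. That is right, but it does not cure the sentence. The one-arm wording and the actual-group rule are already fixed in the protocol, and a plan that follows it would inherit both. Analysing by position received is a known choice for a per-protocol set and matters little if crossovers are excluded; the protocol does not say that they are.

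**Conclusion.** The point holds as a defect of wording with a real consequence for one named analysis. Section 9.2 describes a blind review that must know the arm, names only the intervention arm for additional cases, and groups patients by what they received. The per-protocol analysis of the primary endpoint, which is also sensitivity analysis (1), is therefore open to bias; it is not shown to be biased.

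Under no true effect, 35% good collaterals and 10% to 20% of HDT15 patients removed, the shift in the HDT15 rate runs from about +2 to +6 points (q of 10% to 15%), through zero (q of 35%), to about −2 to −4 points (q of 50%). The shares removed and their outcome rates are assumptions. The rejection rates of 6.2% to 9.8% belong to the favourable cases and to a supportive analysis. They should not be read as the trial's type I error. The primary modified intention-to-treat test and the sample size of 118 are not affected.

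**What to change.** In section 9.2:

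- Delete the clause that places additional cases in the intervention group.
- State that major deviations are judged by the same pre-set criteria in both arms, with the list itself left to the statistical analysis plan.
- State what the review is blind to. Tilt data reveal the allocation, so the workable safeguard is that reviewers do not see the ASITN/SIR grades and that the list of excluded patients is closed before grades are merged with allocation.
- Replace the actual-group sentence: receipt of the other arm's position is a major deviation leading to exclusion from the per-protocol set, so that no patient is moved to the other arm.

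Sensitivity analysis (3) can stay as the openly one-arm analysis it is, reported as such.

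The cost is wording only. A few more control patients may leave the per-protocol set, with a small loss of precision in that analysis.
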